## What are the proposed outcome measures?

### a. Primary outcome

The pain response to heelstick determined by physiological and behavioral reactions to a painful event (Premature Infant Pain Profile (PIPP) scores) will be compared between co-bedding and standard care groups.

### b. Secondary outcomes

The physiological recovery in response to heelstick determined by the length of time for heart rate and oxygen saturation to return to normal (baseline), heart rate variability, hormonal stress response, frequency of 24% sucrose administration, and the response of the twin not receiving the painful procedure when his/her twin undergoes a heelstick procedure will be compared between co-bedding and standard care groups.

### c. Other outcomes

Clinical stability (incidence of apnea or bradycardia, and need for supplemental oxygen prior, during and following (i.e. recovery period) heelstick, the number of painful procedures experienced by the neonate prior to the heelstick procedure, infection rates, and caregiver error will be compared between the groups.

The measurement of the main variables of the study relies on three strategies: video recording of facial actions, monitoring of cardio-respiratory measures and oxygen saturations, collection of salivary cortisol and chart review (Table 1).

**Table 1 T1:** Key variables, measures proposed, data sources, and time of administration

Variables	Measures	Method/Sources	Time of administration
Pain response	Premature Infant Pain Profile (PIPP)	Videotape of facial responses	Baseline, warming heelstick and recovery

Physiologic recovery	Heart rate, Oxygen saturation	Somté software	Baseline, warming heelstick and recovery

Heart rate variability	Cardiac monitoring	Somté software	Baseline, warming heelstick and recovery

Hormonal stress response	Cortisol	Sorbette oral swab	Prior to heelstick (basal) and 20 minutes after (stress) the heel stick

Frequency of 24% sucrose administration	Count	Chart medication record, confirmed with videotape recording	2 minute prior and during intervention

Co-twin Response	All measures identical to the twin undergoing heelstick, except sucrose count	Identical measures, except sucrose count	Baseline, warming heelstick and recovery

Safety surveillance	Caregiver error Infection rate	Institutional adverse event and infection control surveillance	Quarterly

Clinical Stability	Supplemental oxygen Incidence of apnea Bradycardia	Chart review	Baseline, warming heelstick and recovery

## Sample Size

Previous studies examining the effect of maternal contact or the effect of sucrose on pain response during heelstick have revealed a greater than 2 point difference in PIPP scores [48,53,61,66]. In those studies the intervention (i.e. maternal skin-to skin contact or sucrose administration) were compared to a usual care group that received no form of pain relieving intervention. As practice guidelines now indicate, it is anticipated that all twins regardless of group assignment will receive 24% sucrose prior to undergoing heelstick. Since it is known that sucrose has a large effect on pain response, the intervention of co-bedding will be considered an additional comfort measure. A one-point additional decease in PIPP scores would therefore be considered clinically significant.

We based our PIPP score assumptions on previous studies which reported PIPP scores of 10.7 (2.3) vs. 12.9 (2.5) from a study on kangaroo skin-to skin care versus incubator care in preterm infants 32-36 weeks of gestational age [61] and PIPP scores 8.9 (*CI *7.9-9.9) versus 10.7 (*CI *9.6-11.8) in preterm infant 28-31 6/7 weeks of gestational age. Based on these reported 0.5 and 0.6 standard deviation pain scores [66] and the reported values in the above studies, we used a conservative standard deviation estimate of 2.0 as our proposed study population will encompass both groups of infants. Sample size was calculated using a 2-sided alpha error of 0.05 and a power of 80 percent. We designed the study to detect a difference of 1 point or greater change (SD 2.0) in the PIPP scores. One hundred and twenty-eight infants would be required to identify this variation in the PIPP scores if such a difference is in fact caused by co-bedding. With this sample size, we will also have over 95% power to detect a greater than 15 second mean difference in physiological recovery (heart rate and oxygen saturation) between groups. In a recent study of skin-to-skin care [66], the time to return to baseline heart rate following the application of the plaster signifying the end of the procedure was significantly different, 123 seconds (*CI *103-142) for the Kangaroo Mother Care condition and 193 seconds for Incubator condition (*CI *158-227, *p *< .00001). Since all infants will receive 24% sucrose, we do not expect that the differences seen in time to recovery will be this large. Therefore, by using the larger sample, and conservatively accounting for the use of regression techniques, our study will recruit 128 participants (64 sets of twins, 32 assigned to the co-bedding group and 32 to the standard group).

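### The planning SD of 2.0 is called conservative but lies below both SDs the protocol prints (2.3 and 2.5), and the 0.5 and 0.6 it calls SDs are standard errors; power at 128 infants is about 61–68%, not 80%.

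*Protocol article*

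**What the plan says.** The Sample Size section of the protocol article draws on two earlier studies. For infants of 32–36 weeks it cites "PIPP scores of 10.7 (2.3) vs. 12.9 (2.5" (closing bracket cut from the quote). For infants of 28 to 31 6/7 weeks it cites means with intervals: "PIPP scores 8.9 (*CI *7.9-9.9) versus 10.7 (*CI *9.6-11.8" (likewise cut). It continues "Based on these reported 0.5 and 0.6 standard deviation pain scores", adds that the reported values were also considered, and concludes: "we used a conservative standard deviation estimate of 2.0 as our proposed study population will encompass both groups of infants".

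The design statement is "We designed the study to detect a difference of 1 point or greater change (SD 2.0) in the PIPP scores", with "Sample size was calculated using a 2-sided alpha error of 0.05 and a power of 80 percent". The result is 128 infants, 64 per arm. The same section treats a 1-point additional reduction as the clinically significant amount.

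**The concern.** There are two separate faults.

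- **Wrong label.** The younger study is quoted with confidence intervals for means. The values 0.5 and 0.6 are what those interval widths imply for the standard error of a mean, not for the spread between infants. Sample size depends on the spread between infants.
- **Wrong direction.** A conservative planning SD sits at or above the values found in the sources. Here 2.0 sits below both SDs that the section prints.

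The SD is the only variance input to the calculation. If it is too small, the trial has less than the stated 80% power for the difference it calls clinically significant, and a null result could be read as stronger evidence against co-bedding than it is.

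**Working it through.** **Inputs, all from the Sample Size section:** difference 1 point; SD 2.0; two-sided alpha 0.05; 64 infants per arm; printed SDs 2.3 and 2.5; intervals 7.9–9.9 and 9.6–11.8. Two readings are assumed. The intervals are 95% (no level is printed). The bracketed 2.3 and 2.5 are SDs (no label is printed; if they were standard errors, the individual SDs would be larger still).

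**1. The plan's own figure.** A two-sample t-test with standardised difference 1/2.0 = 0.5 needs 63.8 per arm, so 64 per arm and 128 in total. Power at 64 per arm is 80.1%. The stated number reproduces exactly, with no reserve in it for regression adjustment, dropout or twin pairing.

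**2. What 0.5 and 0.6 are.** Standard error = half-width / 1.96.
- (9.9 − 7.9)/2 = 1.0, and 1.0/1.96 = 0.51
- (11.8 − 9.6)/2 = 1.1, and 1.1/1.96 = 0.56

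These round to 0.5 and 0.6. As a cross-check, suppose they were SDs of individual scores. The sample size giving intervals this wide would be (1.96 × 0.5/1.0)² = 0.96 and (1.96 × 0.6/1.1)² = 1.14, about one infant per condition, which is not possible.

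**3. What the younger study's SD could be.** SD = standard error × √n, and n is not given. An SD of 2.0 corresponds to n = (2.0/0.510)² = 15.4 and (2.0/0.561)² = 12.7. So the SD exceeds 2.0 if n is above about 13–15 per condition (about 15–18 if the intervals used t quantiles). Over a range of n:

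| n per condition | implied SD |
|---|---|
| 10 | 1.6–1.8 |
| 16 | 2.0–2.2 |
| 20 | 2.3–2.5 |
| 30 | 2.8–3.1 |
| 60 | 4.0–4.3 |

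This study therefore neither supports nor refutes 2.0 until its n is known.

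**4. Power at the printed SDs.** The pooled value is √((2.3² + 2.5²)/2) = 2.40. Normal approximation: power = Φ(1/(SD × √(2/64)) − 1.96). For SD 2.3 this is Φ(1/0.4066 − 1.96) = Φ(0.50) = 69.1%; the t-test gives 68.5%. The t-test results are:

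| SD | power at 128 infants | total N for 80% power |
|---|---|---|
| 2.0 | 80.1% | 128 |
| 2.3 | 68.5% | 170 |
| 2.4 | 64.7% | 184 |
| 2.5 | 61.2% | 200 |

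**5. Detectable difference.** With 64 per arm, 80% power goes with a standardised difference of 0.5. In points that is 0.5 × 2.3 = 1.15 and 0.5 × 2.5 = 1.25.

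All of this treats the 128 infants as independent.

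**The case against.** **The planned analysis may leave a smaller residual SD.** The analysis section compares means before and after treatment, accounts for stratification and allows regression adjustment. This is the best defence, and it stands as a possibility. To bring 2.3 or 2.5 down to 2.0, the adjustment would have to explain 1 − (2.0/2.3)² = 0.24 or 1 − (2.0/2.5)² = 0.36 of the variance. The protocol claims no such reduction; it derives 2.0 from the reported values.

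**The younger study may have a smaller SD.** This also stands. A reader might infer that 2.0 lies below every SD the document supports. That is certain only for 2.3 and 2.5, since a small n in the younger study would give an SD of 2.0 or less.

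**Mixing gestational ages need not raise the SD.** A reader might infer that combining the two groups can only increase it. That does not hold. With illustrative SDs of 1.7 and 2.4 in equal shares, the within-stratum SD is √((1.7² + 2.4²)/2) = 2.08. A 2-point gap between stratum means adds 1.0 to the variance and gives 2.31, still below 2.4, and a stratified analysis would largely remove that gap.

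**The mislabelling may not be what produced 2.0.** The text does not say how 2.0 was reached, so the causal link is not shown. The power result does not need it.

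**The arithmetic is right.** True: 128 follows from the stated inputs. The fault is in the SD chosen and how it is described.

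**Conclusion.** The point holds in this form: 0.5 and 0.6 are standard errors called standard deviations, and 2.0 is not conservative against the two individual-score SDs the section prints. At those SDs the trial has 61.2% to 68.5% power for a 1-point difference, which is 80.1 − 68.5 = 11.6 to 80.1 − 61.2 = 18.9 percentage points below the plan's own calculation. The detectable difference at 80% power is about 1.15 to 1.25 points.

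The relabelling rests on the intervals being 95%. The power figures rest on 2.3 and 2.5 being SDs, on independent infants, and on no variance reduction from adjustment. They do not depend on the younger study. Because pairs are randomised together, any twin-pair design effect is a further, separate loss that is not counted here.

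**What to change.** In the Sample Size section:

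- Call 0.5 and 0.6 standard errors, and convert them to SDs using the cited study's sample size.
- Remove the description of 2.0 as conservative.
- Either restate power (about 61–68% for 1 point) or detectable difference (about 1.15–1.25 points at 80% power) for SDs of 2.3–2.5, or keep 2.0 and justify it by a stated residual-variance reduction, with R-squared of about 0.24–0.36 and its source.

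Enrolment can stay at 64 pairs and the analysis is unchanged. The cost is a few sentences and a less favourable stated power.

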## What is the proposed type and frequency of analysis?

Analysis and inference will be based on the intention-to-treat principle. Efforts will be made to ensure that follow up is complete for all subjects and that there are no missing values for any of the subjects for any variable. Blinding of independent coders will be retained until after the analysis is completed. Baseline characteristics of study subjects will be contrasted to ascertain that randomization has in fact produced comparable groups with respect to all variables that effect pain response and physiologic stability. The primary outcome of interest will be the pain response of the infant experiencing a tissue breaking procedure while co-bedding with his/her twin when compared to a twin infant experiencing a tissue breaking procedure receiving standard care (alone in incubator or crib). This analysis will compare the means in the two groups before and after treatment and contrast the mean difference between groups using 95 percent confidence intervals and a p value. The stratified nature of the randomization will be accounted for in the analysis. Also, since twin pairs will be randomized together (i.e. to co-bedding or standard care), the analysis will be corrected for potential non independence of outcomes between twin pairs This will involve appropriate variance adjustment which will be carried out using Generalized Estimating Equations (GEE) procedures using SAS software (Proc Genmod, SAS 8.2, SAS Institute Inc. Cary, NC) [77]. If differences are noted in baseline characteristics, inferences will be made based on observed and (linear regression) adjusted differences between groups. Analysis for secondary outcomes will be done in an identical fashion as pain response and recovery by comparing the mean changes in the two groups before and after treatment and contrasting the mean differences between groups using 95 percent confidence intervals and a p value.

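### The 80% power is worked out for one PIPP score per infant, but the primary analysis is worded as a before-after contrast, for which no SD or correlation is given

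*Protocol article*

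**What the plan says.** **Sizing (Protocol article, Sample Size).** The target is set clinically: "A one-point additional decease in PIPP scores would therefore be considered clinically significant". The error rates follow: "Sample size was calculated using a 2-sided alpha error of 0.05 and a power of 80 percent". The design statement is "We designed the study to detect a difference of 1 point or greater change (SD 2.0) in the PIPP scores", which leads to 128 infants, or 32 twin pairs per arm. The SD comes from two published comparisons. One gives means of 10.7 and 12.9 with SDs of 2.3 and 2.5. The other gives means of 8.9 and 10.7 with confidence intervals. From these the section concludes "we used a conservative standard deviation estimate of 2.0 as our proposed study population will encompass both groups of infants".

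**Outcome (What are the proposed outcome measures?, Primary outcome).** The pain response to heelstick, measured by PIPP scores, is compared between the two groups. No change from an earlier score is mentioned.

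**Analysis (What is the proposed type and frequency of analysis?).** Directly after naming the primary outcome, the section says "This analysis will compare the means in the two groups before and after treatment and contrast the mean difference between groups". It then says that the secondary outcomes are handled identically to pain response, by comparing mean changes before and after treatment.

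**Timing.** Table 1 lists PIPP at baseline, warming, heelstick and recovery. The follow-up section places baseline 1-2 minutes before the heelstick. The Co-bedding care section requires at least 24 hours of co-bedding before the heelstick.

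**The concern.** A power figure belongs to one analysis of one quantity. Here the SD describes how PIPP scores vary between infants in one condition, while the analysis wording describes how much each infant's score moves from before to after. The two spreads are linked through the before-after correlation and the SD of the before score, and the protocol states neither. The word *change* in the sizing sentence does not close the gap, because none of the values cited there is a change.

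The trial's ability to detect its own one-point target is at stake. If the pre-stick score is only weakly related to the heelstick score, subtracting it adds noise and power falls below 80%. If the two are strongly related, power rises above 80%. The protocol does not let a reader tell which.

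The timing raises a second issue. By the time of the baseline PIPP, the co-bedded infants have already had the intervention for at least a day. If co-bedding lowers the pre-stick score too, a change contrast subtracts that part of the effect.

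**Working it through.** **Inputs from the protocol:** difference 1 point, SD 2.0, two-sided alpha 0.05, 64 infants per arm.

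**Step 1. Reproduce the plan's figure.** For a two-sample t test with n per arm, the noncentrality is δ / (σ·√(2/n)). With δ = 1, σ = 2.0 and n = 64 this is 1 / (2.0 × 0.1768) = 2.83. The critical value on 126 degrees of freedom is 1.979. Power is 80.1%; 63 per arm gives 79.5%. So 64 per arm, 128 in total, is exactly the stated size. The calculation uses one value per infant and contains no correlation.

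**Step 2. The SD of a change.** With SDb for the before score, SDa for the after score and ρ for their correlation:

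SD of change = √(SDb² + SDa² − 2·ρ·SDb·SDa).

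This equals SDa only when ρ = SDb / (2·SDa). With both SDs at 2.0 that means ρ = 0.5. With SDb = 1.0 and SDa = 2.0 it means ρ = 0.25.

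**Step 3. Power for the change contrast.** Same test, 64 per arm, 1 point, SDa = 2.0. The values of ρ and SDb are assumptions, because the protocol gives neither.

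| SDb | ρ | SD of change | Power |
|---|---|---|---|
| 2.0 | 0 | 2.83 | 51% |
| 2.0 | 0.3 | 2.37 | 66% |
| 2.0 | 0.5 | 2.00 | 80% |
| 2.0 | 0.7 | 1.55 | 95% |
| 1.0 | 0 | 2.24 | 71% |
| 1.0 | 0.25 | 2.00 | 80% |
| 1.0 | 0.5 | 1.73 | 90% |

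Worked line: SDb = 2.0 and ρ = 0.3 give √(4 + 4 − 2.4) = √5.6 = 2.37; the noncentrality is 1 / (2.37 × 0.1768) = 2.39, and power is 66%.

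All rows take the infants as independent, as the reproduced figure does, so they isolate this one issue.

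**Step 4. Effect of the timing.** Suppose co-bedding lowers the heelstick-phase score by 1 point and the pre-stick score by e points. The change contrast then estimates 1 − e, while the contrast of heelstick-phase scores estimates 1. The protocol gives no value for e. It is zero only if co-bedding does nothing to the score before the stick.

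**The case against.** **The change analysis is not firmly fixed.** The primary outcome section describes only a comparison of scores. *Before and after treatment* is awkward wording for a treatment that starts a day or more before the first PIPP listed in Table 1, and the sizing sentence can be read as a one-point shift between groups. On that reading the sizing and the outcome agree. This has weight: the protocol describes its primary contrast in two ways. It does not remove the point, because the analysis section states the before-after comparison for the primary outcome and repeats it as mean changes when it calls the secondary analyses identical.

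**Model detail may sit in an analysis plan.** The choice between a change, a heelstick score and a baseline-adjusted score often does. A baseline-adjusted analysis at SD 2.0 would have at least the stated power at any correlation, provided that co-bedding leaves the baseline score unaffected. But the point is not that detail is missing. It is that the SD source and the analysis wording in this document do not match.

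**Stronger readings.** A reader might infer that the SD of the change differs from 2.0, that the trial is underpowered, or that the sample size was miscalculated. The protocol supports none of these. The SD of change can equal 2.0 at plausible inputs, power can lie on either side of 80%, and the stated arithmetic is correct for the quantity it uses. Nothing in the text favours a low correlation over a high one.

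**Conclusion.** The point holds as an unsupported power statement. The 80% belongs to a between-arm comparison of one PIPP score per infant with SD 2.0, and it is not justified for the before-after contrast that the analysis section describes.

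The size cannot be given as one number. With SD 2.0 at both times, power runs from 51% to 95% as the assumed correlation goes from 0 to 0.7, and 80% is met at 0.5. With a before-SD of 1.0, it runs from 71% to 90% for correlations from 0 to 0.5. These ranges take 2.0 as right for a heelstick score, twins as independent and all 128 infants as measured. The mismatch remains even when all of that is granted.

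The loss of effect through the pre-stick score is a possibility that follows from the timing. The protocol has no figure from which to estimate it.

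**What to change.** In the analysis section, name the between-arm contrast of the heelstick-phase PIPP score as the primary analysis, with site and gestational-age stratum as terms in the GEE model. This is the quantity that the primary outcome section describes and the Sample Size section sizes, so the 80% then refers to the stated analysis on its own assumptions. It also avoids subtracting a score taken after co-bedding has begun. The sizing sentence should drop the word *change*.

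If the change contrast is kept, say which two PIPP phases it uses and restate the power with the SD of that change over a stated range of correlations.

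Either route costs a sentence or two and needs no extra data. The downside of the second is that the stated power may become less favourable.

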### c. Study population

The source population consists of all twin pairs admitted to a tertiary level NICU at the IWK Health Centre, Halifax, Nova Scotia and St. Justine Hospital, Montreal, Quebec, who are considered medically stable and who require at least one medically indicated heelstick for blood procurement.

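### The 128-infant sample size is the figure for independent infants, so with twin pairs randomised together power falls below the stated 80% for any positive within-pair correlation

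*Protocol article*

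**What the plan says.** The Sample Size section of the protocol article gives a complete calculation.

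- Error rates: "Sample size was calculated using a 2-sided alpha error of 0.05 and a power of 80 percent".
- Target: "We designed the study to detect a difference of 1 point or greater change (SD 2.0) in the PIPP scores".
- Result: "One hundred and twenty-eight infants would be required to identify this variation in the PIPP scores".
- Recruitment: "our study will recruit 128 participants (64 sets of twins, 32 assigned to the co-bedding group and 32 to the standard group".

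The only allowance it mentions comes just before the final number: "conservatively accounting for the use of regression techniques, our study will recruit 128 participants". No within-pair correlation, design effect or inflation factor is given.

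The analysis section (*What is the proposed type and frequency of analysis?*) states that both twins of a pair go to the same group. It adds that "the analysis will be corrected for potential non independence of outcomes between twin pairs", through a variance adjustment with generalized estimating equations (GEE). It also says that the stratification will be taken into account; the Randomization section stratifies by gestational age and by site.

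**The concern.** The sample size and the planned analysis rest on different assumptions. The first counts 128 separate observations. The second treats them as 64 clusters of two and adjusts the variance for correlation within each cluster. If twins resemble each other in pain response, the planned analysis has less information than the sample size credits it with.

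The reference to regression techniques adds to the problem, because it suggests a safety margin that the numbers do not show.

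One point is the difference that the protocol itself calls clinically significant. A reader who takes the 80% at face value would give a null result more weight against a 1-point effect than the design supports.

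**Working it through.** **Inputs.** From Sample Size: difference 1.0, SD 2.0, two-sided alpha 0.05, power 80%, 64 pairs, 32 per arm. From the analysis section: pairs randomised together and a correction for within-pair correlation. The ICC is not in the document, so the values below are assumptions.

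**Step 1. Reproduce 128.** For independent observations, the normal approximation is

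n per arm = 2 × (1.96 + 0.842)² × 2.0² / 1.0² = 62.8, rounded up to 63 (126 in total).

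The two-sample t-test needs 63.77 per arm, rounded up to 64, which gives 128. Its power is 0.8015 at 64 per arm and 0.795 at 63. So 128 is the smallest equal-arm total that reaches 80% for independent infants, and nothing is left over. Other settings do not explain it: the normal approximation gives 100 for a one-sided test and 170 for 90% power.

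**Step 2. Look for an allowance.** Required before the sentence on regression techniques: 128. Recruited after it: 128. Added: 128 − 128 = 0.

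**Step 3. Put the pairs in.** With two infants per cluster and whole clusters allocated, the design effect is 1 + (2 − 1) × ICC = 1 + ICC. In terms of pair means:

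- SD of a pair mean = 2.0 × √((1 + ICC)/2)
- standard error of the group difference = SD of a pair mean × √(2/32)
- test: t with 62 degrees of freedom (64 pairs less 2)

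Example at ICC 0.3: the SD of a pair mean is 2.0 × √0.65 = 1.612. The standard error is 1.612 × 0.25 = 0.403, the noncentrality is 1/0.403 = 2.48, and power is 0.685.

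At ICC 0 the difference detectable with 80% power is 1.006 points. It scales with √(1 + ICC); at ICC 0.1, for instance, 1.006 × √1.1 = 1.055.

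| Assumed ICC | Design effect | Effective infants (128 / design effect) | Power for 1 point | Detectable at 80% power (points) |
|---|---|---|---|---|
| 0 | 1.0 | 128.0 | 0.795 | 1.01 |
| 0.1 | 1.1 | 116.4 | 0.756 | 1.06 |
| 0.2 | 1.2 | 106.7 | 0.720 | 1.10 |
| 0.3 | 1.3 | 98.5 | 0.685 | 1.15 |
| 0.5 | 1.5 | 85.3 | 0.623 | 1.23 |

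The first row is 0.795 and not 0.8015 only because the pair-level test has 62 degrees of freedom and the infant-level test has 126. The normal approximation gives slightly higher values throughout: 0.807, 0.769, 0.733, 0.699 and 0.637. The pattern is the same, and even an ICC of 0.05 takes that approximation below 80%, to 0.788.

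**Step 4. The extreme.** At ICC 1, 128 infants carry the information of 64, and power is about 0.50.

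**The case against.** **The ICC is unknown.** The protocol speaks only of potential non-independence, and at ICC 0 power is about 80%. A reader might infer that the trial definitely lacks 80% power, or lacks it by a particular amount. The documents do not support that, because the shortfall depends on an ICC that they do not give. The direction is clear for any positive value, and the protocol gives reasons to expect one: twins share gestational age and unit, and where possible the same nurse.

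**Adjustment may recover precision.** The analysis accounts for the strata and allows covariate adjustment if baseline differences appear. That could remove some between-pair variance, which is why the relevant ICC is the residual one. But no gain is quantified and none is built into 128.

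**The inference itself is protected.** The analysis corrects the variance and reports 95% confidence intervals, so an interval will show directly whether 1 point is excluded. This stands. The flaw is in the power statement and does not make the planned analysis invalid. It does not make the 80% correct either.

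**The regression phrase is ambiguous.** It follows the recovery-time calculation and refers to using the larger sample, which may mean only the larger of two requirements. Calling the phrase false would go too far. What can be shown is that it is unsupported, since no increase is visible.

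**Number of heelsticks.** The Study population section describes twin pairs "who require at least one medically indicated heelstick for blood procurement". A reader might infer that one heelstick per pair is enough, and hence a much larger loss of power. The wording does not settle this. The co-bedding and standard-care sections describe a heelstick for all infants, and the protocol gives no figure for how many will lack one. At most, 128 assumes that every infant contributes a study heelstick.

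**Conclusion.** The point holds in conditional form. The 128 is exactly the independent-infant t-test size and shows no allowance for pairing or for regression. Power for a 1-point difference is therefore below the stated 80% for any positive residual within-pair correlation. Over an assumed ICC of 0.1 to 0.5, power runs from about 0.76 to 0.62, and the detectable difference from about 1.06 to 1.23 points.

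These figures rest on the protocol's SD of 2.0, on 32 complete pairs per arm with every infant contributing an outcome, and on a pair-mean t-test standing in for the GEE analysis. The true loss cannot be fixed from the document.

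**What to change.** In Sample Size:

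1. State that 128 is the requirement for independent infants. Then give power for a 1-point difference, and the difference detectable with 80% power, for 64 pairs with design effect 1 + ICC over a stated ICC range such as 0 to 0.5. Give the basis for that range, and say that the ICC is the one remaining after the strata.
2. Delete the phrase saying that 128 conservatively accounts for regression techniques, or correct it to say what was allowed for and by how much.
3. If wished, add one sentence that the figures assume a study heelstick from every infant.

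The cost is wording only. Enrolment, conduct and the GEE analysis stay as they are; the stated power becomes less favourable.

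### The stated power of over 95% for a 15-second recovery difference is not supported by the only recovery data quoted, which imply roughly 0.1 to 0.6

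*Protocol article*

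**What the plan says.** All of this is in the Sample Size section of the protocol article.

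- Primary outcome: "Sample size was calculated using a 2-sided alpha error of 0.05 and a power of 80 percent", and "We designed the study to detect a difference of 1 point or greater change (SD 2.0) in the PIPP scores".
- Size of the trial: "128 participants (64 sets of twins, 32 assigned to the co-bedding group and 32 to the standard group", which is 64 infants per arm.
- Recovery time: "we will also have over 95% power to detect a greater than 15 second mean difference in physiological recovery". No SD for recovery time and no source for one is given.
- The next sentence gives the only recovery data in the article, from a cited skin-to-skin study: "123 seconds (*CI *103-142) for the Kangaroo Mother Care condition" and "193 seconds for Incubator condition (*CI *158-227, *p *< .00001". The size of that study is not stated.
- The text then expects smaller recovery differences here than in that study, because every infant will receive sucrose.
- For the pain score, the same study is quoted as "PIPP scores 8.9 (*CI *7.9-9.9) versus 10.7 (*CI *9.6-11.8". The article then describes 0.5 and 0.6 as that study's standard deviations.

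**The concern.** A power of more than 95% for 15 s is a strong statement about a variable whose quoted means are 123 and 193 s and whose confidence intervals are 39 and 69 s wide. An interval for a mean reflects the standard error. The spread between infants, which determines power, is larger by the square root of the sample size. If the quoted study is any guide to that spread, 64 infants per arm cannot give the stated power.

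Time to physiological recovery is the first secondary outcome listed and appears in the Abstract. A reader who trusts the sentence would take the trial to be well able to detect a 15 s difference, and could give a non-significant result more weight than it can bear.

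**Working it through.** **Inputs** (all from the Sample Size section unless marked)

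- Two-sided alpha 0.05; 64 infants per arm; difference 15 s; claimed power above 0.95.
- Cited recovery intervals: 103–142 s and 158–227 s. Assumption: they are 95% intervals for a mean.
- The cited study's n is not given. Assumption: a range from 10 to 60, with smaller values tested separately.

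**1. The primary sample size reproduces.** n per arm = 2 × (1.96 + 0.84)² × 2.0² / 1² ≈ 63 by normal approximation and 64 by the t-test, so 128 in total, as stated. This treats infants as independent.

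**2. SD needed for the recovery claim.** SD ≤ 15 / [(1.96 + 1.645) × √(2/64)] = 15 / 0.637 = 23.5 s; 23.4 s with the exact t-test.

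**3. Standard errors from the quoted intervals.**

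- Skin-to-skin: half-width (142 − 103)/2 = 19.5 s; SE = 19.5/1.96 = 9.95 s.
- Incubator: half-width (227 − 158)/2 = 34.5 s; SE = 34.5/1.96 = 17.6 s.
- Root mean square of the two: √[(9.95² + 17.6²)/2] = 14.3 s.

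**4. SDs and power.** Pooled SD = 14.3 × √n. If the intervals were built with a t quantile, 1.96 is replaced by t on n − 1 degrees of freedom: SD = 28.0 × √n / t, where 28.0 is the root mean square half-width. Power is from the two-sample t-test with 64 per arm. The last column is √(2/64) times the t-test equivalent of (1.96 + 0.84), about 0.50, times the SD. In each range the two values come from the 1.96 and t-quantile conversions.

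| n of cited study | Pooled SD (s) | Power for 15 s | Difference detectable with 80% power (s) |
|---|---|---|---|
| 10 | 39–45 | 0.46–0.58 | 20–23 |
| 20 | 60–64 | 0.26–0.29 | 30–32 |
| 30 | 75–78 | 0.19–0.20 | 38–39 |
| 60 | 109–111 | 0.12 | 54–55 |

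**5. How small would the cited study have to be?** With 1.96, power is 0.986 at n = 2 and already 0.925 at n = 3. With t quantiles, the more generous conversion, it is 0.96 at n = 5 (SD 22.6 s) and 0.88 at n = 6. So the claim needs n of 5 or fewer.

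**6. The quoted p-value excludes that.** Take the most favourable case, a paired t-test with perfectly correlated conditions. The SE of the difference is then (34.5 − 19.5)/t. At n = 5 it is 15/2.776 = 5.4 s, so the statistic is 70/5.4 = 13.0 on 4 degrees of freedom and p ≈ 0.0002. The p-value first falls below 0.00001 at n = 9, where power for 15 s is 0.50–0.64.

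**7. Most favourable SD.** Using the smaller (skin-to-skin) SD in both arms, power is 0.76–0.87 at n = 10 and 0.47–0.52 at n = 20. With t quantiles it falls below 0.95 from n = 9.

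**8. What reproduces the claim.** If the standard errors are entered as SDs, power is 0.998 with 17.6 s and above 0.999 with 9.95 or 14.3 s. The pain-score text shows the same confusion for the same study: half-widths of 1.0 and 1.1 divided by 1.96 give SEs of 0.51 and 0.56, the values the article labels as SDs.

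**9. Pairing.** Twins are randomised together, and the analysis section plans a correction for this. A positive within-pair correlation ρ multiplies the variance by 1 + ρ when both twins contribute. No value is given. At the extreme, ρ = 1 (32 units per arm), power is about 0.26 at n = 10 and 0.15 at n = 20 (1.96 conversion, normal approximation).

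**The case against.** **The source of the SD is unknown.** The article does not say that the 15 s figure was derived from the skin-to-skin study. That study is quoted in the next sentence, to explain why a smaller difference is expected. The compliance section mentions the team's own pilot study and a larger ongoing trial, and any source with an SD of about 23 s or less would support the claim. This stands in part. A reader might infer that the SE-for-SD swap is established, or that it is the only way to reach the figure. The documents do not show that: no recovery SD is printed, and nothing says whether the team's other studies measured recovery time. It remains that the only data offered point the other way.

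**The pain-score mislabel did no harm.** True. The primary calculation used SD 2.0, not 0.5 or 0.6, and 128 reproduces from it. The mislabel makes a similar slip for recovery time plausible, no more.

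**Sucrose for all infants could reduce the spread as well as the difference.** Possible, but the article says only that the difference will shrink. The SD would have to be roughly half the n = 10 value, or little more than a third of the n = 20 value.

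**The consequences are limited.** This stands. The planned analysis reports mean differences with 95% confidence intervals, which would show the imprecision. A reader might also infer that the trial is very unlikely to detect 15 s; with n near 10 power is about one half, so that is too strong over the whole range. The lowering of power by pairing assumes a positive correlation that the article does not quantify.

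**Conclusion.** The power statement is wrong as written, judged against the data printed beside it. It requires an SD of about 23 s or less; the quoted intervals imply a pooled SD of about 39–45 s if the cited study had 10 infants and about 109–111 s if it had 60. Power for 15 s is then between about 0.58 and 0.12, before any loss from pairing, instead of more than 0.95.

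This rests on three assumptions: the quoted intervals are at the 95% level, the cited study's n is between 10 and 60, and its spread is a fair guide to this trial's. The second matters least to the conclusion, because every n consistent with the quoted p-value (9 or more) puts pooled power at 0.64 or below. An SE/SD mix-up is the likely explanation but is not proven.

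The point should be fixed but does not threaten the design. The outcome is secondary, and the sample size of 128 is reached from the pain score without it.

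**What to change.** State the SD assumed for recovery time and its source. If the source is the skin-to-skin study, convert its confidence intervals to SDs using that study's n. Then replace the claim of 95% power for 15 s with the resulting power, or with the difference detectable at 80% power, allowing for an assumed within-pair correlation. As a guide, the unclustered detectable difference is about 20–23 s at n = 10, 30–32 s at n = 20 and 54–55 s at n = 60. If another source supplied an SD near 23 s, cite it and give the value. In the same edit, relabel the 0.5 and 0.6 quoted for the pain score as standard errors.

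The cost is wording only. The stated figure becomes less favourable; the sample size, outcomes and analysis do not change.
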